## Abstract

**Background:**

Fresh frozen plasma (FFP) is the accepted standard treatment for clotting factor replacement in bleeding patients during or immediately after cardiac surgery. In the United Kingdom prothrombin complex concentrate (PCC) is not licensed in this setting, although it is being used in Europe because it has a higher concentration of clotting factor levels, and it can be administered rapidly and in small volume, resulting in less volume overload during cardiac surgery.

**Methods:**

PROPHESY is a pragmatic, single-centre, open-label, randomised, controlled pilot trial that will assess whether it is feasible to perform a large trial in the future that will compare PCC versus FFP in patients who are bleeding (not on warfarin) and who require blood transfusion. Over a 15-month period, 50 patients will be randomised to PCC versus FFP if they develop active bleeding within 24 h of cardiac surgery and for whom the clinician has decided to administer FFP for treatment of bleeding. Standard laboratory and point-of-care assessments will be performed as per routine practice, and additional research blood samples will be taken at three time points to assess haemostasis. Subjects will be assessed daily up to hospital discharge or 30 days or death (whichever occurs first) and will be seen in follow-up for 90 days after surgery to assess for thromboembolic complications and hospital re-admission since discharge. Quality-of-life assessment will be performed pre-surgery and at 90 days post-surgery. We will also perform qualitative research with clinical experts and patients to explore the understanding of and experience with the interventions, as well as adherence to study procedures and protocol.

**Discussion:**

There have been no randomised controlled trials that have compared the safety and efficacy of FFP versus PCC in cardiac surgery patients who are bleeding. This pilot study will assess if individual components of a large trial are deliverable to assess the safety and efficacy of the two blood products in the future.

**Trial registration:**

EudraCT, 2018-003041-41; ClinicalTrials.gov, NCT03715348. Registered on 29 July 2018.

## Background

Approximately 30,000 cardiac procedures are performed each year in the United Kingdom, and it is estimated that approximately 10% of all blood supplied by the National Blood Service is used during these procedures. Bleeding after cardiac surgery that requires blood transfusion is associated with significant morbidity and mortality, resulting in substantial costs to healthcare systems [1]. The national comparative audit in the United Kingdom in 2011, which incorporated data from 66% of all UK cardiac centres, showed that the overall blood transfusion rate was high across all procedures, with fresh frozen plasma (FFP) being administered in over 20% of patients undergoing valve replacement or repair surgeries and in 30% of patients undergoing combined coronary artery bypass graft + valve repair/replacement surgeries [2].

FFP is the accepted standard treatment for replacement of clotting factors in bleeding patients undergoing cardiac surgery; yet, in a recent Cochrane review only 1 study out of 14 trials (*n* = 738 participants) identified has evaluated the efficacy of FFP in bleeding patients, and this was underpowered to determine outcomes in mortality [3]. Taking into consideration that blood transfusion is not without risks, other haemostatic agents, such as prothrombin complex concentrate (PCC), are being explored by clinicians for management of bleeding, including in the peri-operative phase for patients undergoing cardiac surgery. Potential advantages of PCC over FFP include increased concentration of clotting factors leading to faster and more sustained reversal of coagulopathy, improved ease and speed of administration, reduced fluid volume (20–40 ml compared with up to 1000 ml with FFP), and reduced incidence of immunomodulatory side effects.

However, to date there have been no randomised controlled trials (RCT) that have compared the clinical efficacy and safety of PCC versus FFP in bleeding cardiac surgery patients who are not taking vitamin K antagonists (e.g., warfarin), and this was highlighted in a recent systematic review [4]. Several observational studies have demonstrated that PCC is safe in this setting and that its administration is associated with reduced blood transfusion requirements, albeit with no difference in other outcomes [5, 6]. However, clinical equipoise and the lack of high-quality evidence means that an RCT is required to determine how PCC compares with FFP. Prior to such a trial, a pilot study is required to determine if a large-scale RCT is possible, and this is the hypothesis of our single-centre RCT.

## Methods

### Study design

The study design is a single-centre (Barts Health NHS Trust), open-label, non-blinded, pragmatic, pilot RCT (see Fig. 1 for study flowchart).

**Fig. 1 Fig1:**
[figure not shown]
Study flowchart

### Aim and objectives

The aim of this study is to determine if it is feasible to deliver a large trial in the future that will compare FFP versus PCC in cardiac surgery patients who are bleeding within 24 h of surgery.

#### Primary objective

The primary objective is to evaluate the recruitment rate, defined as the proportion of subjects who consent to the study (of all those eligible) and receive the intervention.

#### Secondary objectives

The following are secondary objectives of this study:
Assess the delivery of different components of the trial, protocol compliance and violation, and the ability to collect outcome dataCompare the impact of FFP and PCC on the haemostatic capacity of bleeding patients through the use of standard clotting tests and other global clotting testsObtain input from patients, members of the public and healthcare professionals on the design/running of the large trial, as well as identify the most important primary/secondary outcomes for the larger trial

#### Primary outcome

The primary outcome will be the proportion of participants who receive the intervention within 24 h of surgery, out of all eligible participants.

#### Secondary endpoints

The secondary endpoints of the study are as follows:
Time to administration of study drug (PCC) or control (FFP) to patient, defined as time in minutes from telephoning laboratory to first administration to patientProportion of patients for whom clinical outcome data were collected up to 90 days, or death, whichever occur firstProportion of patients who consent and are randomised within 24 h of surgeryProportion of patients who consent and are not randomised within 24 h of surgeryProportion of patients for whom timing of administration and completion of intervention(s) are documentedProportion of patients in whom there is protocol adherence and protocol violationProportion of patients who do not consent to intervention but agree to consenting of their de-identified data for up to 24 h after surgeryObtain data on event rates in both groups to help estimate the sample size for the large trial. Event rates will be assessed at 24 h and 7, 14, 21 and 30 days, or upon discharge or death, whichever is first. Clinical outcomes assessed at these time points include those described under ‘Study assessment’, such as total days in intensive care unit, any organ failure, thrombosis, acute transfusion reaction, infections, duration of organ support and mortality.

### Study population

A total of 50 patients will be randomised over a 15-month period, with follow-up at 90 days or death, whichever occurs first. Consent will be obtained from all patients prior to participation in the trial.

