### Statistics

#### Sample size calculation

Over a 15-month period, we expect 638 patients to be eligible. This would allow us to estimate a consent rate of 30% within a 95% confidence interval of ± 3.5%. Assuming that 30% of the eligible patients consent, we will have a sample of 191 patients on the basis of which to estimate the proportion of consented patients who bleed and are administered FFP/PCC. From the national and local cardiac audit data, the rate of FFP transfusion in the eligible study patients is just over 30%, so we have estimated that 30% of consented patients will go on to develop bleeding during surgery that requires FFP transfusion. A sample size of 191 would allow us to estimate a proportion of 30% within a 95% confidence interval of ± 6.5%. On the basis of the above 30% rate, around 57 patients would be randomised within 15 months, giving an expected final sample size of 50 patients completing the study after allowing for 10% drop-out or loss to follow-up. This sample would be analysed for assessment of the secondary endpoints. No formal interim analysis for efficacy is planned. Numbers recruited, eligibility and consent rates will be considered by the data and safety monitoring committee (DSMC). Safety analysis including reporting of adverse events will be undertaken biannually for review by the DSMC. Other interim analysis may be undertaken at the request of the DSMC. Tables will be prepared by the study statistician.

The primary analysis will use data from the eligible patient population (for consent rate estimation) and the consenting patients (for estimation of the percentage who are randomised and receive study treatment). The proportion of patients who agree to collection of their de-identified data for up to 24 h after surgery will be obtained to analyse the population of eligible patients who do not consent to enter the main trial. The intention-to-treat population will be used to analyse secondary endpoints relating to the delivery of the intervention, clinical outcome data and haemostatic capacity of patients. Full details of the statistical considerations are given in the study statistical analysis plan.

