## Trial status

Protocol V2.0, 27 November 2018. Start date of subject recruitment: 1 March 2019. Project recruitment completion date: 30 June 2020.

The study was peer-reviewed by three independent experts as part of the BHF funding application and underwent Barts Heart Centre independent peer review. The study protocol has been reviewed by the Barts Cardiovascular Clinical Trials Unit (CVCTU) Scientific Committee and the Blizard Institute, Medicines and Healthcare products Regulatory Agency (MHRA) and NHS research ethics committees.

CVCTU will oversee the management and conduct of the trial and will be responsible for pharmacovigilance and safety reporting, coordination of trial committees, statistical analysis and reporting, and database management and case report form (CRF) design. The study sponsor will be responsible for trial monitoring. When the research trial is complete, it is a sponsor requirement that the records be kept for a further 20 years in a secure, long-term storage facility as per the sponsor policy.

Data will be captured in REDCap, a web-based electronic database, for all study participants, and the database will be held on a secure server at Queen Mary University of London (QMUL). Participants eligible for the study will be given a screening number, and this number will be used to identify them throughout the study duration. The screening number will be identified on all electronic case report forms (eCRFs) and study documentation (e.g., questionnaires, laboratory reports, enrolment and dispensing logs). Only authorised users approved by the chief investigator (CI) will have access to the REDCap electronic database, and each user will be assigned specific user roles and rights. Sponsor representatives and CVCTU team members will have read-only access to the data. The study research nurse will be the primary person with delegated responsibility for data entry and CRF completion. The transfusion laboratory team will have access to the eCRF to complete randomisation. The CI will have overall responsibility for data captured in the eCRF and be able to review, lock and electronically sign the completed eCRFs.

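### The protocol randomises 50 patients in two places, but expects about 57 randomised and 50 completing in a third; the two cannot both hold

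*Protocol article*

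**What the plan says.** The number to be randomised appears in three places in the protocol article.

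- Abstract, Methods: "Over a 15-month period, 50 patients will be randomised to PCC versus FFP".
- Study population: "A total of 50 patients will be randomised over a 15-month period".
- Sample size calculation: "around 57 patients would be randomised within 15 months", followed by "giving an expected final sample size of 50 patients completing the study after allowing for 10% drop-out or loss to follow-up".

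The last section builds its figure from a fixed window: "Over a 15-month period, we expect 638 patients to be eligible". It takes 30% of these as consenting (191) and 30% of the consenters as bleeding and needing plasma. It states 95% half-widths of 3.5 points for the consent rate and 6.5 points for the second proportion.

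The Primary outcome section takes the patients who receive the intervention within 24 h of surgery as a proportion of all eligible participants. The Trial status section gives the recruitment dates: "Start date of subject recruitment: 1 March 2019. Project recruitment completion date: 30 June 2020".

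**The concern.** The same figure, 50, is the number randomised in two sections and the number completing in a third, for the same 15 months and with a 10% loss between the two stages. A reader cannot tell which is the planned size, or whether recruitment ends at a count or at a date.

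In an efficacy trial this might be a matter of wording only. Here recruitment is what the pilot measures. The patients randomised supply the numerator of the primary outcome, and the eligible patients over the window supply its denominator. If site staff read 50 as a ceiling, one of these would be altered by the rule rather than by what is feasible, and the altered proportion would go into the planning of the large trial.

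**Working it through.** **Inputs** (all from the Sample size calculation unless noted): 638 eligible in 15 months; consent rate 30%; bleeding and plasma rate among consenters 30%; loss 10%; number randomised 50 (Abstract, Study population) or about 57.

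**Step 1. Reproduce the plan's own figures.**
- Consented: 638 × 0.30 = 191.4 (stated 191).
- Randomised: 191 × 0.30 = 57.3 (stated around 57).
- Completing: 57 × 0.90 = 51.3 (stated 50).
- Half-width = 1.96 × √(p(1 − p)/n) with p = 0.30. For n = 638 it is 3.56 points (stated 3.5). For n = 191 it is 6.50 points (stated 6.5).

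The Sample size calculation therefore agrees with itself, apart from rounding.

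**Step 2. Put 50 randomised through the same loss.**
- 50 × 0.90 = 45 completers, 5 short of the stated 50.
- 50 / 0.90 = 55.6, so 50 completers need 56 randomised.

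The figure of 50 cannot be both the number randomised and the number completing.

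**Step 3. What would follow if 50 acted as a cap.** The protocol does not state a cap, so this step is conditional. At the planned rates the chance of at least 50 randomisations among 638 eligible patients (binomial, 0.30 × 0.30 = 0.09) is 0.86, so a cap would usually be reached.

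*(a) Screening and consent also end at the 50th randomisation.*
- Consented: 50 / 0.30 = 166.7. Eligible: 166.7 / 0.30 = 555.6.
- Time: 15 × 555.6 / 638 = 13.1 months.

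| Proportion | Planned n | Planned half-width | n at stop | Half-width at stop | Change |
|---|---|---|---|---|---|
| Consent among eligible | 638 | 3.56 | 556 | 3.81 | 0.25 |
| Randomised among consented | 191 | 6.50 | 167 | 6.96 | 0.46 |

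Half-widths and changes are in percentage points.

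*(b) Screening and consent run the full window, but randomisation is capped.* The denominators stay at 638 and 191, and the numerator is cut off. This assumes that every randomised patient receives the intervention in time.
- Among eligible: 50/638 = 7.8% instead of 57/638 = 8.9%.
- Among consented: 50/191 = 26.2% instead of 57/191 = 29.8%.

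**Step 4. Window length.** 1 March 2019 to 30 June 2020 is 10 months of 2019 plus 6 of 2020, so 16 months, not 15. At 638/15 = 42.5 eligible per month, 16 months gives about 681 eligible and 681 × 0.09 = 61 randomised.

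**The case against.** The strongest reply is that no section says that screening, consent or randomisation ends at the 50th patient. All three statements are framed by a 15-month period, and 57 is worded as an expected yield, not a target. The stated precision rests on 638 eligible and 191 consented. If recruitment simply runs for 15 months with no cap, that precision is untouched whichever number is right. The primary analysis uses the eligible and consenting patients; the 50 completers serve the secondary endpoints only. All of this stands, and it makes the effects in step 3 conditional.

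Three stronger readings are tempting, and the document does not support them.

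- *The trial will miss its stated precision.* This needs a stopping rule that the protocol does not contain. Even with it, the loss is 0.25 and 0.46 points.
- *The loss arithmetic is wrong, because 57 × 0.90 is 51 and not 50.* Both figures are rounded expectations that differ by about one patient. That is rounding.
- *A monthly recruitment rate would be distorted.* The Primary objective and Primary outcome sections define recruitment as a proportion of eligible patients. No monthly rate is a stated outcome.

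The dates in the Trial status section are operational, and a sixteenth month would slightly improve precision, so that mismatch is minor.

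The reply does not remove the conflict itself. Two sections state without qualification how many patients will be randomised, and the section that derives the sample size gives a different number for the same period.

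**Conclusion.** The contradiction is real and needs no assumption beyond the protocol's own 10% loss. The number randomised is 50 in the Abstract and the Study population section and about 57 in the Sample size calculation. If 50 are randomised, about 45 complete and not 50.

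The effect on the primary result depends on how 50 is read. With a fixed window and no cap there is none. With a cap, either the half-widths widen to about 3.8 and 7.0 points, or the proportion among eligible patients falls from 8.9% to 7.8% because of the rule. These sizes assume that the planned 30% and 30% rates hold and, for the second, that every randomised patient is treated in time. The consequences are modest, but the number affected is the one the pilot exists to estimate, so it should be settled in the text. The 15- versus 16-month difference is secondary.

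**What to change.** 1. In the Abstract and the Study population section, replace the figure of 50 randomised so that both agree with the Sample size calculation: about 57 expected to be randomised, about 50 completing.
2. State that recruitment runs for the fixed window on which 638 and 191 are based, with no cap at 50 randomised.
3. If the sponsor prefers to keep 50 randomised, restate the expected completers as about 45, say whether screening and consent continue after the 50th randomisation, and give the resulting precision.
4. Reconcile the 15-month window with the 16 months between the recruitment dates. If 16 is meant, rescale 638, 191 and 57.

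Items 1 and 2 cost a few words and need no more patients than the 57 the Sample size calculation already expects. That is about seven more than the Abstract and Study population figure, so anything planned around 50 randomised, such as product supply or sample storage, should be checked against 57.

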#### Inclusion criteria

The study will include adult patients (aged > 18 years) who are able to give consent and undergoing elective or non-elective cardiac surgery, excluding procedures listed below under ‘Exclusion criteria’.

#### Exclusion criteria

Exclusion criteria are inability to consent; patients refusing blood transfusion for any reason; first time isolated coronary artery bypass graft; first time isolated aortic valve replacement (excluding active endocarditis); thoraco-abdominal surgeries; minor surgeries that do not involve cardiopulmonary bypass; use of warfarin within 4 days; use of direct oral anticoagulants (i.e., dabigatran, rivaroxaban, apixaban or edoxaban) within 48 h or 72 h, depending on estimated glomerular filtration rate; inherited bleeding disorder; pregnancy; known or suspected allergy to FFP, octaplasLG (Octapharma, Lachen, Switzerland) or PCC; known or suspected allergy to heparin, sodium citrate dihydrate, sodium dihydrogen phosphate dihydrate and glycine; history of heparin-induced thrombocytopenia; immunoglobulin A (IgA) deficiency with known antibodies against IgA; documented venous thromboembolism in the last 3 months; documented antiphospholipid syndrome; severe protein S deficiency; and participation in another clinical trial where the patient has received an investigational medicinal product in the last 3 months.

For women of childbearing age (< 50 years old) a urine pregnancy test will be performed for eligibility purposes. There will be no other study-specific screening procedures.

To determine the bleeding rate, routine clinical data will also be collected for up to 24 h for (1) eligible participants who have consented to take part in the study but are not randomised because they did not develop bleeding and (2) eligible participants who have not consented to take part in the main study but have consented to the collection of de-identified routine data.

### Randomisation process

The pragmatic nature of the study means that the decision whether to administer the intervention will be based on clinicians’ judgement, so that when a patient is actively bleeding within 24 h of surgery and a clinician has decided that FFP is needed to treat the bleeding, the patient will be randomised by the transfusion laboratory to either a single dose of FFP (fresh frozen plasma or octaplasLG) or 4-factor PCC (octaplex; Octapharma) using a web-based electronic database. Block randomisation will be used to ensure balance of treatments. The algorithm will be written by the study statistician using the ralloc command in Stata software (StataCorp, College Station, TX, USA), and a randomisation list will be produced. In the United Kingdom it is recommended that, as a variant Creutzfeldt-Jakob disease risk reduction measure, individuals born after 1 January 1996 should be transfused non-UK plasma, and this has been the practice since 1999 [7]. At the study site, octaplasLG is the standard of care for management of such patients who are bleeding. Doses of intervention will be calculated according to subject weight and as per the dosing schedules below.

**Table Taba:** 

Subject weight	FFP or octaplasLG
≤ 60 kg	3 units
61–90 kg	4 units
> 90 kg	5 units
Subject weight	octaplex (IU)
≤ 60 kg	500 (one vial)
61–90 kg	1000 (two vials)
> 90 kg	1500 (three vials)

If the subject continues to bleed after this first single dose of study treatment, standard care for the treatment of bleeding will continue as per hospital protocol, and this may include having additional FFP. However, no further PCC will be administered to these subjects.

#### Study assessments

Subjects will have laboratory assessments with standard routine care tests and thromboelastography. Research blood samples will also be taken at three time points (pre-intervention and 1 h and 24 h post-intervention) to perform a more detailed analysis of haemostatic capacity of subjects (see Table 1 in Appendix, Additional file 1). Samples will be stored at − 70 °C ± 10 °C within 4 h of collection until they have been analysed, and no longer than 3 years after their collection. After analysis all samples will be destroyed. Samples will also be destroyed if the participant withdraws consent.

**Table 1 Tab1:** Assessments of randomised subjects

Study Procedure	Screening pre-operatively	Prior to surgery (time 0)	Prior to randomisation – intervention	1 h post-study intervention	24 h post-surgery	Days 7, 14, 21	Day 30 (discharge/death)	Day 90 (discharge/death)
Visit windows	− 14 days	Day 0	Day 0	Day 0	Day 1	+/− 1 day	+/− 2 days	+/− 7 days
Screening - assess eligibility (includes urine pregnancy test)	X							
Informed consent	X							
Patient characteristics	X							
Assessment by surgical team	X							
Assessment by anaesthesiologist	X							
Blood tests^a^ – FBC	X		X	X	X			
Blood tests^a^ - group and screen samples	X	X						
Blood tests^a^ – liver and renal function tests	X				X			
Routine coagulation tests (PT, aPTT and fibrinogen)^a^	X		X	X	X			
Additional clotting assays^b^			X	X	X			
Thromboelastographic assessment^a^			X	X	X			
Inform transfusion laboratory of need for FFP			X					
Randomisation and intervention – PCC or octaplasLG /FFP			X					
Time of intervention (start and stop)			X					
Weekly ICU assessment					X	X		
Thromboembolic AE/SAE				X	X	X	X	X
Transfusion AE/SAE				X	X	X	X	
Hospital re-admission since discharge								X
Quality of life – EQ-5D	X							X
90-Day survival status - end of study form (telephone or clinic visit)								X

*Abbreviations: AE* adverse events, *aPTT* activated partial thromboplastin time, *EQ-5D* EuroQol 5-dimension quality of life scale, *FBC* full blood count, *FFP* fresh frozen plasma, *ICU* intensive care unit, *PCC* prothrombin complex concentrate, *PT* prothrombin time, *SAE* serious adverse events

Clinical data that will be collected include age, sex, ethnicity, previous medical history, drug history, type of surgery and date/time of intervention. For those who have received intervention, daily and weekly (24 h and 7, 14, 21 and 30 days, or upon discharge, or death, whichever is first) assessments will be performed for amount of blood lost through the chest drains, blood components transfused (red blood cells, FFP, platelets and cryoprecipitate), any other haemostatic agents administered (such as recombinant factor VIIa, fibrinogen concentrate), total days in intensive care unit (level 3), high-dependency units (level 2), any organ failure (e.g., acute lung injury, acute respiratory distress syndrome, renal failure, liver failure), thrombosis (arterial and venous thrombosis), acute transfusion reaction, infections, duration of organ support (i.e., ventilatory support, cardiovascular support, and renal replacement therapy), and mortality. At 90 days or death, whichever is first, the following data will be collected: mortality, re-hospitalisation, thromboembolic event (arterial and venous), number of days alive and out of hospital since operation, and quality-of-life questionnaire.

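### The third research sample is timed from the intervention in the text but from surgery in Table 1, so following the table lets the dose-to-sample interval vary from 24 h down to 0 h

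*Protocol article*

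**What the plan says.** The protocol article, Study assessments, describes the research sampling in one sentence: "Research blood samples will also be taken at three time points (pre-intervention and 1 h and 24 h post-intervention". All three times are tied to the intervention.

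Table 1, in the same section, has a row "Additional clotting assays^b" with three marks: before randomisation and intervention, 1 h after the study intervention, and "24 h post-surgery". The visit window of that last column is Day 1. The columns for the intervention and for the 1 h sample are labelled Day 0. No column is headed 24 h after the intervention.

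The time of dosing is not fixed relative to surgery. The Abstract says patients are randomised "if they develop active bleeding within 24 h of cardiac surgery", and Randomisation process says this happens "when a patient is actively bleeding within 24 h of surgery and a clinician has decided that FFP is needed to treat the bleeding". The Primary outcome section likewise counts treatment within 24 h of surgery.

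The samples serve the second of the three Secondary objectives, the comparison of FFP and PCC on haemostatic capacity. The Statistics section assigns that analysis to the intention-to-treat population.

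**The concern.** The text and the table give two different times for the same research sample. The heading does not read as loose shorthand, because the column beside it is explicitly timed from the study intervention; the table itself distinguishes the two clocks.

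The late sample is meant to show how haemostatic capacity stands a day after FFP or PCC. If staff draw it by the table, each patient contributes a measurement at a different interval after the product, and patients treated late contribute one taken almost immediately. If some staff follow the text and others the table, the timing varies further. Recording the times lets the interval be calculated afterwards, but a sample drawn at the wrong time cannot be retaken. With about 50 patients there is little information to spare.

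**Working it through.** The protocol article states no figure on this point, so there is none to reproduce. The check is a comparison of the two clocks.

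**Inputs**
- Third research sample: 24 h after the intervention (Study assessments text) or 24 h after surgery (Table 1).
- Second research sample: 1 h after the intervention (text and table agree).
- Dosing window: t from 0 to 24 h after surgery (Randomisation process; Primary outcome).
- Randomised patients: 50 (Study population), taken as 25 per arm. Equal arms are an assumption, consistent with the stated aim of balance.
- Distribution of t: not given. Two assumed distributions show the range.

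**Formulas**, for a dose at t hours after surgery
- Table 1: the third sample falls 24 − t hours after the dose.
- Text: the third sample falls 24 + t hours after surgery.
- The 1 h sample falls t + 1 hours after surgery.
- The two versions of the third sample are therefore t hours apart, at most 24 h.

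| Dose, h after surgery (t) | Table 1: h from dose to third sample (24 − t) | Text: third sample, h after surgery (24 + t) | 1 h sample, h after surgery (t + 1) |
|---|---|---|---|
| 0 | 24 | 24 | 1 |
| 4 | 20 | 28 | 5 |
| 12 | 12 | 36 | 13 |
| 18 | 6 | 42 | 19 |
| 23 | 1 | 47 | 24 |
| 24 | 0 | 48 | 25 |

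At t = 23 the table's third sample and the 1 h sample fall at the same moment (24 h after surgery). For t above 23 the table's third sample comes first.

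**Spread of the interval under Table 1**
- Dosing uniform over 0–24 h (assumed): mean 24 − 12 = 12 h; SD 24/√12 = 6.9 h; about 50% of intervals under 12 h and about 4% under 1 h (1/24).
- Mostly early dosing (assumed: exponential with mean 4 h, truncated at 24 h; simulated): mean 20.1 h; SD 3.8 h; about 5% under 12 h and under 0.1% under 1 h.
- Dosing during surgery: t is close to 0, and the two clocks nearly coincide.
- Text anchor: 24 h for every patient, SD 0.

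**Balance between arms**

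The standard error of the chance difference between arms in mean interval is SD × √(2/25). This gives 6.93 × 0.283 = 2.0 h under uniform dosing and 3.83 × 0.283 = 1.1 h under early dosing. The expected difference in time from surgery to randomisation is zero, because allocation is random at the moment of need.

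**The case against.** The strongest objection is that little of the late comparison is lost.

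- **Validity.** A reader might infer that following Table 1 makes the late comparison uninterpretable or biased. The protocol article does not support that. Patients are randomised when the product is needed and "Block randomisation will be used to ensure balance of treatments", so the time from surgery to randomisation is balanced in expectation. A sample at a fixed time after surgery still gives a valid randomised comparison. The pre-intervention and 1 h samples are unaffected. Table 1 also records "Time of intervention (start and stop" times, so the true interval can be derived wherever the sample time is kept. This objection stands.
- **Size.** The sample size section plans on the basis that "30% of consented patients will go on to develop bleeding during surgery that requires FFP transfusion", and the Discussion considers bleeding before chest closure. Both suggest that many doses come early, when the two clocks differ little. A third sample that precedes the 1 h sample needs a dose after hour 23, an edge case. This stands as a limit on size. It does not remove the contradiction, because the permitted window is 24 h and the Discussion also contemplates bleeding into chest drains in intensive care.
- **Routine tests.** A reader might extend the contradiction to routine coagulation tests and thromboelastography, which share the table's last column. The text gives these no time anchor, the Abstract says standard assessments follow routine practice, and their footnote differs from that of the research assays. No contradiction is shown for them.
- **Drain loss and transfusion.** A reader might infer that the 24 h clinical counts also run from surgery and so include losses before randomisation. Table 1 has no row for drain loss or components, and the Secondary endpoints and Study assessments sections say only 24 h. The origin is unstated, but it is not shown to be wrong.
- **Unseen material.** The footnotes to Table 1 and Additional file 1 are not shown and may settle the timing. They do not change the fact that the article gives two times for one sample.

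**Conclusion.** The inconsistency is real and confined to the time anchor of the third research sample. If Table 1 is followed, the interval from dose to sample is 24 − t hours and ranges from 24 h to 0 h, instead of a fixed 24 h. Its average depends on dosing times that the protocol article does not give: about 12 h (SD 6.9 h) if uniform, about 20 h (SD 3.8 h) if mostly early, and close to 24 h if dosing is during surgery.

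The consequence is a late haemostatic comparison that is unbiased between arms but mixes post-dose intervals and does not estimate the 24 h post-dose effect described in the text. This touches one secondary objective of a feasibility pilot; the primary outcome, receipt of the intervention among eligible patients, is untouched. Severity: moderate.

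**What to change.** - In Table 1, give the research clotting assays a column headed 24 h after the intervention, matching the text, and carry the same wording into the sampling instructions.
- Let the visit window for the intervention and the 1 h sample read Day 0–1, so that patients treated late in the window fit the schedule.
- Routine tests and thromboelastography may stay at 24 h after surgery. Any of them used to compare PCC with FFP should share the post-intervention anchor or be analysed with the actual time since dose, which requires the sample time to be recorded.
- State the time origin of the 24 h clinical assessments in Secondary endpoints and Study assessments.

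The cost is an edit to the table and the sampling instructions. The number of research samples stays at three. Late-treated patients would have the last one drawn up to 48 h after surgery (24 + 24), as the text already implies. The change has to be made before sampling starts.
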